#### Hardware

The VR system that will be used for visualization on-site is the HTC Vive headset (HTC Corporation, China). This VR headset uses stereoscopy, a technique to create the illusion of depth from the analysis of two images obtained through binocular vision. The lighthouse tracking system (Valve corporation, USA) and the HTC Vive Tracker will be also used to recognize body movements. Four Vive Trackers can be attached to the patient's wrist and ankles (one at each end) to enable body tracking while leaving the patient's hands free, which will be required for some exercises. This system allows for including virtual feet in the virtual environment that represent the movements of the patient's feet in real time.

The HTC Vive has some limitations to be used at home, such as specific hardware requirements. Therefore, the Oculus Quest headset will be used instead, which is a fully standalone headset that includes two ergonomic controllers. The virtual environments have been adapted for the Oculus Quest headset. Since the Oculus Quest headset cannot detect the patient's feet, exercises in which feet had to be identified were modified. Both the HTC Vive and Oculus Quest headsets increase the patient's sense of immersion into virtual environments and allow the system to execute a cause-effect response between exercise storytelling and the patient's response. Both headsets incorporate a system that warn the patient when she/he approaches the physical limits of the rehabilitation area, so that the patient is aware of them.

#### Software

The program consists of two virtual environments that are designed and developed to allow the patient to perform motor and cognitive rehabilitation exercises in an interactive game-based setting. The patient will be required to perform specific tasks in order to accomplish a mission in two different environments: a *fantasy medieval world* (Figure 2) and a *deserted island* (Figure 3). These virtual environments were designed to combine a variety of rehabilitation exercises in different positions (sitting, standing or lying) with gaming elements, making the otherwise monotonous exercises more competitive and motivating.

**Figure 2 F2:**
[figure not shown]
Screen shots of the *fantasy medieval world* virtual environment.

**Figure 3 F3:**
[figure not shown]
Screen shots of the *deserted island* virtual environment.

The patient will practice various movements (kick forward, kick back, triple flex, paddle) while performing the required tasks. Some examples of the tasks in the virtual environments are fighting against flying dragons that throw fireballs that patients have to return by kicking them, learning how to use a sword in a fencing class, or rowing in a small boat to escape from pirates who attack the island. The movements incorporated in these tasks were suggested by the multidisciplinary team and were mainly intended to decrease fatigue, and improve spasticity control, balance and coordination. The cognitive components of the tasks are aimed at training several cognitive domains, such as attention and short-term memory. For instance, one of the tasks is an alchemy class in which the patient is required to cook a recipe with the exact same ingredients in a cauldron. Before each task starts, an avatar called Guía will explain to the patient in detail the steps required to complete the task, while another avatar called Cidoimos will do a physical demonstration on how to perform the task, so that the patient can copy the specific position and movements made by Cidoimos in order to accomplish the goal explained by Guía (see Supplementary Material 1). These avatars will serve as a support tool for patients to conduct the exercises that will be previously explained and supervised by the physiotherapist.

The environments were implemented using the Unreal Engine 4 (Epic Games, USA) game engine, which is compatible with both HTC Vive and Oculus Quest headsets. A main user interface was developed for the HTC Vive to allow the physiotherapist to: (i) include the list of patients and record the date of their last session, (ii) customize a list of exercises for each session according to the patient level and progress, (iii) consult the exercises completed and not completed, (iv) keep a record of total time spent in the session and specific time spent on each exercise.

During each on-site VRR session, the physiotherapists will supervise whether patients correctly perform all the exercises. The exercises have been classified in three categories according to their physical and cognitive difficulty (A, B, or C, corresponding to a low, medium and high level of difficulty). The level of difficulty and the type and number of physical exercises will be selected based on the functional status of each patient. The difficulty of the cognitive tasks will be automatically adjusted according to patient progress. Thus, a patient could simultaneously perform physical exercises of medium difficulty and cognitive tasks of high difficulty. The accuracy with which the patient performs the task will constitute the measure of game performance. Positive feedback will be provided by the system before, during, and after task performance to boost patient motivation. Patients will be encouraged to contact any member of the study team in case of discomfort, for any question regarding the study protocol, or in case of technical problems.

### Outcome Measures

Table 1 lists the study data collection overview, including primary and secondary outcome measures. Study variables will be collected on an electronic case report form. The assessments are described below.

**Table 1 T1:** Data collection overview.

**Data collection**	**Screening visit (V_**0**_)**	**Baseline visit (V_**1**_)**	**Post-rehabilitation on-site visit (V_**2**_)**	**Post-rehabilitation at-home or study completion visit (V_**3**_)**
Informed consent	x			
Inclusion and exclusion criteria	x			
Sociodemographic data: age, sex, educational level and profession	x			
Clinical history: time from MS diagnosis, type of MS, use of DMTs, previous EDSS score, clinical rehabilitation history	x			
Satisfaction with VRR: USEQ	x	x	x	x
Adherence to rehabilitation		x	x	x
ClinROs: EDSS, 9-HPT, T25-FW, 6 MWT, MAS, BBS		x	x	x
PROs: MSIS-29, EuroQoL-5D, MFIS, Barthel index, MSWDQ-23, BDI-FS, HADS, PSFS, MSNSQ		x	x	x
Rao's BRB		x	x	x
Discomfort		x	x	x

#### Primary Outcome Measures

The primary outcome is satisfaction at 6 months of VRR program initiation. Satisfaction is assessed by using the USEQ, which is a 6-item questionnaires using a 5-point Likert scale (29). The primary variable is the USEQ total score, which ranges from 6 (lower satisfaction) to 30 points (higher satisfaction). To calculate this total score, all of the questions are considered to be positive, except for Q5, which is considered to be negative. The numerical value of the positive questions is used to calculate the score. The negative question subtracts the numerical value of the response from 6 and then adds this result to the total score (for instance, if the patient selects two in Q5, then four is added to the total score). The questions and their scores are shown in Table 2.

**Table 2 T2:** The User Satisfaction Evaluation Questionnaire (USEQ).

**Question**	**Response (not at all-very much)**
1. Did you enjoy your experience with the system?	1 2 3 4 5
2. Were you successful using the system?	1 2 3 4 5
3. Were you able to control the system?	1 2 3 4 5
4. Is the information provided by the system clear?	1 2 3 4 5
5. Did you feel discomfort during your experience with the system?	1 2 3 4 5
6. Do you think that this system will be helpful for your rehabilitation?	1 2 3 4 5

The questions that composed the USEQ come from the set of questions of the Suitability Evaluation Questionnaire (SEQ) that evaluate satisfaction (39). The SEQ is a previously developed 14-item questionnaire designed to test satisfaction, acceptance, and security of use in VRR systems. The SEQ has previously been used in a clinical trial of MS patients receiving VRR conducted in Spain (24).

Probably due to the relatively recent publication of the USEQ (July 2017), no study using this questionnaire in MS patients has yet been published. We selected the USEQ for four main reasons. Firstly, because it has been specifically designed to assess satisfaction with a VRR program. Secondly, because it has been validated in a Spanish population of patients with balance disorders. Thirdly, because the patients considered the questionnaire to be short and easy-to-understand. And lastly, because the questionnaire demonstrated to be reliable and to have adequate internal consistency (α = 0.716) (29).

### Secondary Outcome Measures

#### Rehabilitation Adherence

Adherence to the on-site rehabilitation sessions will be measured by the number of rehabilitation sessions attended. Participants will be contacted by email or phone if they fail to take part in two consecutive rehabilitation sessions. Rehabilitation adherence at home will be measured by the VR system itself in the VRR group, and by the nurses participating in the study who will require patients in the CR group to indicate via email the frequency with which they have conducted the exercises each week.

#### Clinician-Reported Outcomes

A variety of clinician-reported outcomes (ClinROs) will be collected at the baseline visit (V_1_), post-rehabilitation on-site visit (V_2_), and a post-rehabilitation at-home visit or study competition visit (V_3_) by a neurologist unaware of the rehabilitation group allocation. Changes from the baseline visit (V_1_) to month 6 (V_3_) and from the baseline visit (V_1_) to month 1 (V_2_) will be collected as secondary and exploratory variables, respectively. ClinROs were selected on the basis of previous studies of rehabilitation that reported statistically significant improvements by using VRR in disability (17, 18), spasms and spasticity (40), and balance (19, 24, 33).

Disability progression will be evaluated by the EDSS (36), the Nine-Hole Peg Test (9-HPT) (41), the Timed 25-Foot Walk (T25-FW) (42), and the Six-Minute Walk Test (6 MWT) (43). The EDSS (36) assesses 7 functional systems based on a neurological examination. The score ranges from 0 to 10 in 0.5-unit increments that represent higher levels of disability. The 9-HPT (41) tests upper extremity function. Patients will be instructed to place pegs from a container one by one into each of the nine holes of the board as quickly as possible. The score is the average time required in four trials (two trials for each hand). It is one of the three components of the MS Functional Composite (MSFC) disability assessment (42). No specific cut-off score has been validated for MS (44), but a worsening of 20% on all the measures of the MSFC is generally accepted to indicate disease progression. The T25-FW (42) evaluates mobility and leg function performance based on the time until the patient reaches the 25-foot mark (7.62 m). Patients will start at a line on the floor and will be instructed to walk as quickly as possible but safely beyond the second line 25 feet away. The score is the averaged time of 2 trials, and the time limit per trial is 3 min. It is another of the three components of the MSFC disability assessment (42). The 6 MWT (43) measures the distance walked over a span of 6 min. Patients will be instructed to walk at a comfortable pace back and forth along a 60-foot walkway for 6 min (43).

Spasms and spasticity will be assessed by the Modified Ashworth Scale (MAS) (45). This scale measures resistance during passive soft-tissue stretching. It consists of a 5-point nominal scale using subjective clinical assessments of tone ranging from 0 to 4.

Balance will be evaluated by the Berg Balance Scale (BBS) (46). The BBS assesses 14 daily life activities with scores ranging from 0 to 4. The cumulative results categorize patients into three groups: ≤20 for wheelchair users, >20 ≤ 40 for those walking with assistance, and >40 ≤ 56 for those who are independent.

#### Patient-Reported Outcomes

Several patient-reported outcomes (PRO) will be also collected at the baseline visit (V_1_), post-rehabilitation on-site visit (V_2_), and post-rehabilitation at-home visit or study competition visit (V_3_). Changes from the baseline visit (V_1_) to month 6 (V_3_) and from the baseline visit (V_1_) to month 1(V_2_) will be collected as secondary and exploratory variables, respectively. PROs were selected on the basis of previous studies of rehabilitation that reported statistically significant improvements by using VRR in HRQoL (22, 26, 47, 48), fatigue (19, 49), and ADL (26). The evaluation of depression and anxiety after VRR has received little attention, despite the fact that the prevalence of these disorders has increased (50). To evaluate depression and anxiety, we selected questionnaires that have shown to be valid measures of these disorders in MS (51, 52). As far as we know, no previous study has evaluated work status and self-perceived changes after a VRR program. Therefore, questionnaires specifically designed for MS patients in this regard (46, 47) were considered the most appropriate to be used here (53, 54). The Spanish for Spain version of all PRO will be used, and all PRO assessments will be collected by an electronic device.

HRQoL will be assessed by the Multiple Sclerosis Impact Scale (MSIS-29) (55) and the EuroQol EQ-5D-5L (56). The MSIS-29 (55) measures the physical and psychological impact of MS from the patient's perspective. It is composed of 29 items grouped in two scales: physical and psychological. Each item is assessed by the patient using a 5-point Likert scale ranging from 1 (not at all) to 5 (extremely). Each of the two scales are scored by summing the responses across items, then converting them to a 0–100 scale where 100 indicates greater impact of disease on daily function (worse health). The MSIS-29 has shown to be one of the most sensitive scales in detecting rehabilitation-induced changes (48). The EQ-5D-5L (56) consists of a five-item descriptive system and a visual analog scale (EQ VAS). The descriptive system consists of five health dimensions (mobility, self-care, usual activities, pain/discomfort and anxiety/depression) and subjects may choose from five response levels (no problems =1, slight problems = 2, moderate problems = 3, severe problems = 4, and unable to/extreme problems = 5), where higher values indicate worse health.

Fatigue will be measured by the Modified Fatigue Impact Scale (MFIS) (57). The MFIS is based on 21-items derived from interviews with MS patients concerning how fatigue impacts their lives. This instrument provides an assessment of the effects of fatigue in terms of physical, cognitive, and psychosocial functioning. The total score of the MFIS ranges from 0 to 84 (physical, 0 to 36; cognitive, 0 to 40; and psychosocial, 0 to 8).

ADLs will be evaluated by the Barthel index (58). The Barthel index is a 10-item ordinal scale that uses ten variables describing ADLs and mobility. Each item is rated on this scale with a given number of points assigned to each level or ranking. A higher number is associated with a greater likelihood of being able to live at home with a degree of independence.

Work status will be assessed by the Multiple Sclerosis Work Difficulties Questionnaire (MSWDQ-23) (53, 59). The MSWDQ-23 is a brief valid measure of workplace difficulties that can predict both employment outcomes and expectations in patients with MS. It examines work difficulties across three broad domains: psychological/cognitive barriers (11 items), physical barriers (eight items), and external barriers (four items). Participants are asked to rate how often they experienced each difficulty as a result of their MS over the past 4 weeks on a 5-point Likert-type scale, with response options ranging from 0 = “Never” to 4 = “Almost Always.”

Depression will be tested by the Beck Depression Inventory-Fast Screen (BDI-FS) (60). The BDI-FS is a 7-item questionnaire designed to evaluate depression in patients with medical illness (dysphoria, anhedonia, suicidal ideation, and cognition-related symptoms) on a 3-point scale. Scores on the BDI-FS range from 0 to 21, with higher scores indicating more depressive symptoms.

Anxiety will be measured by the Hospital Anxiety and Depression Scale (HADS) (61). The HADS is a 14-item questionnaire designed to evaluate anxiety and depression in patients with medical illness on a 3-point scale. It provides two sub-scales, one for anxiety and one for depression symptoms. Scores for every subscale range from 0 to 21, with higher scores indicating more anxiety and depression symptoms.

Spasm frequency will be evaluated by the Penn Spasm Frequency Scale (PSFS) (62). The PSFS is a two component self-report measure of the frequency of reported muscle spasms commonly used to quantify spasticity. The first component is a 5-point scale assessing the frequency with which spasms occur ranging from 0 to 4. The second component is a 3-point scale assessing the severity of spasms ranging from 1 to 3.

The Multiple Sclerosis Neuropsychological Screening Questionnaire (MSNSQ) (54) will be used for identifying patients at high risk for cognitive impairment in MS.

#### Cognitive Assessment

To test the cognitive performance of the participants, Rao's Brief Repeatable Battery (BRB) will be applied by a neurologist unaware of the rehabilitation group allocation. This battery has shown to be a sensitive measure of cognitive impairment in MS patients (63). It consists of the Selective Reminding Test (SRT), the 10/36 Spatial Recall Test (SPART), the Symbol Digit Modalities Test (SDMT), the Paced Auditory Serial Addition Test (PASAT) and the Word List Generation Test (WGT).

#### Discomfort

Each patient will be asked about the presence of discomfort (e.g., dizziness, vertigo, nausea, headaches, falls, and others) by the physiotherapist after each session. During the at-home rehabilitation period, patients will be instructed to record the occurrence of discomfort, and to report it to the treating neurologist at each study visit. Discomfort will also be assessed by question 5 in the USEQ (see Table 2).

#### Demographic and Clinical Characteristics

Sociodemographic data (age, sex, educational level and profession) and clinical data (time from MS diagnosis, type of MS, use of DMTs, previous EDSS score, and clinical rehabilitation history) will be also collected.

### Data Analysis

Data entered manually will be collected via electronic data capture (EDC) by the site. PRO data will be collected by patients on electronic questionnaires implemented in an electronic device. The data from the questionnaires will be automatically transferred to the EDC system.

### Sample Size Calculations

Sample size calculations were conducted using the Granmo v7.11 software. No previous studies using the USEQ in patients with MS have been performed, so assumptions had to be made for estimation of the sample size. Since the standard deviation (SD) of the USEQ score in MS patients was not available, an estimation based on the maximum variance from the range SD=range/2 was considered. In the particular case of the total score of the USEQ, an estimated SD of 12 (in the most unfavorable case) was used. Considering a SD of 12 units, 32 patients in the VRR group will be sufficient to estimate a population mean of the total score of the USEQ with 95% confidence and a precision of ±4.3 units. A replacement rate of 5% has been anticipated.

Comparisons between the rehabilitation groups (VRR vs. CR) are planned for some secondary and exploratory outcomes. These objectives are assessed by scales or questionnaires that can be transformed to a 0–100 scale. In a scale of this range, a SD of 50 points for the mean of both groups can be assumed by the maximum variance principle. A difference of 20 points in the mean change between the two groups and a correlation coefficient of 0.90 will be assumed for each scale/questionnaire. Accepting an alpha risk of 0.05 and a beta risk of 0.2 in a two-sided test, 16 patients in the CR group and 32 patients in the VRR group are required to recognize a difference equal to or >20 units as statistically significant. A drop-out rate of 5% has been anticipated.

### Statistical Analysis Plan

To address the primary objective, the total score for USEQ in the VRR group with measures of central tendency and dispersion (mean, SD, median, minimum and maximum) will be presented.

To compare mean changes after 6 months of VRR or CR on domains typically affected by MS (HRQoL, fatigue, ADL, work status, depression, anxiety, disability, spasms and spasticity, balance, and cognition) an inferential analysis will be used. For variables that follow a normal (or parametric) distribution, a *t*-test will be used. For variables that do not follow a normal (or parametric) distribution, Mann-Whitney (for unpaired data) or Wilcoxon (for paired data) hypothesis tests will be used. For the analysis of the contingency tables and comparison of proportions and/or frequency distributions, the chi-squared test (or Fisher's exact test where appropriate) will be used. All tests will be 2-tailed, and *p* < 0.05 will be considered significant.

To investigate therapy adherence and discomfort during the VRR program, a descriptive statistical analysis will be performed. Measures of central tendency and dispersion (mean, SD, median, minimum and maximum) will be presented.

The association between clinical and demographic characteristics and patient satisfaction with the VRR program will be calculated using Pearson or Spearman correlation coefficients, as appropriate.

Absent data will not be accounted for and will be considered missing data. No imputation will be done. Parameter estimates and 95% confidence intervals will be reported for the principal quantitative outcomes. The Statistical Package for the Social Sciences (SPSS) software (v 22 or later) will be used to conduct the analysis. Further details of data analysis will be provided in a statistical analysis plan.

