### Intervention

Patients will attend 8 on-site rehabilitation sessions during 4 weeks (2 sessions per week) of ~2 h duration each. The rehabilitation sessions will be conducted by a physiotherapist in groups of a maximum of 4 at the physiotherapy room of the Hospital Universitario de la Princesa in Madrid (Spain). Groups will be formed according to patients' functional level measured by the EDSS (36), resulting in three subgroups (low, medium, or high functional level) in each rehabilitation group (VRR and CR). The number of sessions conducted on site will provide sufficient training to allow patients to continue performing the rehabilitation exercises at home independently.

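### Six-month changes are compared between arms without using the baseline score as a covariate, and the test, and so the effect measure, depends on how each variable is distributed

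*Protocol article*

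**What the plan says.** The Statistical Analysis Plan section of the protocol article describes one between-group analysis for the outcome domains (quality of life, fatigue, daily activities, work, mood, disability, spasticity, balance, cognition). The aim is "To compare mean changes after 6 months of VRR or CR on domains typically affected by MS". The method depends on the distribution: "For variables that follow a normal (or parametric) distribution, a *t*-test will be used", and "For variables that do not follow a normal (or parametric) distribution, Mann-Whitney (for unpaired data) or Wilcoxon (for paired data) hypothesis tests will be used". No covariate or adjusted model appears.

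The Sample Size Calculations section sizes the comparison on the same basis. It takes "a SD of 50 points for the mean of both groups can be assumed by the maximum variance principle" on a 0–100 scale and adds: "A difference of 20 points in the mean change between the two groups and a correlation coefficient of 0.90 will be assumed". The error rates are given as "Accepting an alpha risk of 0.05 and a beta risk of 0.2 in a two-sided test". The result is 16 CR and 32 VRR patients, with 5% drop-out anticipated.

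Table 1 shows the clinician-reported outcomes, the patient-reported outcomes and the cognitive battery collected at V1, V2 and V3, so each has a baseline value. The Statistical Analysis Plan section also promises parameter estimates with 95% confidence intervals for the principal quantitative outcomes, and leaves further detail to a separate statistical analysis plan that is not shown.

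**The concern.** Two features of the stated method work against the comparison it is meant to make.

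First, a raw change score subtracts the whole baseline value, whereas the best linear prediction of the follow-up value (with equal SDs) subtracts only r times it. Unless r is 1, subtraction over-corrects. That costs precision. If the arms differ at baseline by chance, it also moves the estimated difference in the opposite direction. With 16 controls, a moderate chance imbalance on some of the many scales is to be expected.

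Second, the stated aim is a comparison of mean changes, but Mann-Whitney compares the ranks of the changes. For outcomes that fall on that side of the rule, the p-value no longer refers to the quantity the plan says it compares. The effect measure would then vary from scale to scale according to the data. Several scales are ordinal by construction, such as the Modified Ashworth Scale and the Penn Spasm Frequency Scale, so their method can be chosen now.

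At stake are the width of the intervals and the readability of the VRR versus CR results. The primary outcome, a descriptive satisfaction score in the VRR arm, is not affected.

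**Working it through.** **Inputs** (Sample Size Calculations section): SD 50, difference 20, r = 0.90, two-sided alpha 0.05, power 80%, ratio 2:1, drop-out 5%, 16 CR and 32 VRR. I read the correlation as that between baseline and follow-up, and the plan's figure reproduces on that reading. Equal SDs at both visits are assumed. The values r = 0.7 and r = 0.5 are my assumptions, to show the range.

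**1. The plan's own figure.**
- SD of change = 50 × √(2 × (1 − 0.90)) = 22.36.
- CR patients needed = 1.5 × (22.36 × (1.960 + 0.842) / 20)² = 14.7, so 15.
- With drop-out: 15 / 0.95 = 15.8, so 16 CR and 32 VRR.

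The stated size reproduces, which confirms that it rests on an unadjusted change score.

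**2. Variance with baseline adjustment.**
- Change score: 2 × (1 − r) × SD².
- ANCOVA: (1 − r²) × SD².
- Ratio: (1 + r)/2, which is 0.95 at r = 0.90, 0.85 at 0.7 and 0.75 at 0.5.
- Estimating one slope multiplies the ANCOVA variance by about 1 + 1/44 at N = 48, giving 0.97, 0.87 and 0.77.

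**3. Power and precision at 16 versus 32** (difference 20, SD 50 throughout, noncentral t):

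| r | SD change | SD ANCOVA | Power, change | Power, ANCOVA | 95% CI half-width, change / ANCOVA |
|---|---|---|---|---|---|
| 0.90 (plan) | 22.36 | 21.79 | 81.6% | 82.6% | 13.8 / 13.6 |
| 0.7 (assumed) | 38.73 | 35.71 | 37.9% | 42.5% | 23.9 / 22.3 |
| 0.5 (assumed) | 50.00 | 43.30 | 24.9% | 30.9% | 30.8 / 27.0 |

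A simulation of 20,000 trials gave 81.7% and 82.6% at r = 0.90, and 24.7% and 30.7% at r = 0.5.

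**4. Chance imbalance in the baseline score.**
- SE of the baseline difference = 50 × √(1/16 + 1/32) = 15.3 points.
- An imbalance of one SE shifts the change-score contrast by (1 − r) × 15.3: 1.5 points at r = 0.90 and 7.7 points at r = 0.5, against a target difference of 20.
- ANCOVA removes the linear part of this shift for the score that is adjusted. It does not correct imbalance in other characteristics.

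**5. Adding functional level (low, medium, high) to the model.** This uses two more degrees of freedom. At r = 0.90, if functional level predicts nothing beyond the baseline score, power at 16 versus 32 is 80.8%, slightly below the 81.6% of the planned test.

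**The case against.** The strongest reply is that the planned test is conventional, valid and consistent with its own sample-size basis, and that with the plan's r of 0.90 adjustment buys one point of power and 0.2 points of interval half-width. The comparisons are secondary, in a study that calls itself a pilot, and more detail is deferred to an analysis plan that is not shown. Most of this stands and limits the weight of the point. It does not remove it. The tests are already named, so this is a comment on a stated choice and not on missing detail. The r of 0.90 is one assumed value applied to every scale over six months.

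A reader might also infer more than the document supports:

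- **That the results will be biased.** The change-score contrast is unbiased over randomisations. The shift in step 4 arises only given an observed imbalance, and is small at r = 0.90.
- **That adjustment lifts power from just under 80% to the mid or high 80s.** This follows only if the SD of change is held at 22.36 while r falls, which implies a raw SD of about 29 at r = 0.7 and 22 at r = 0.5. The plan states 50.
- **That every secondary outcome can be adjusted.** Adherence and discomfort have no meaningful pre-treatment value and are to be analysed descriptively.
- **That a formal normality test decides the method.** The article does not say how or when normality is judged, so the error rate of any particular test is not evidence about this plan.
- **That outcomes tested by Mann-Whitney will have no interval.** Estimates with 95% intervals are promised for the principal quantitative outcomes. What remains true is that the test and a mean difference would address different quantities.

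**Conclusion.** The point holds as a recommendation on efficiency and consistency in the secondary comparisons; the planned analysis is not invalid. With the plan's inputs, adjusting for the baseline score raises power from 81.6% to 82.6%. If true six-month correlations are lower, the gain is about 5 points at r = 0.7 (37.9% to 42.5%) and 6 points at r = 0.5 (24.9% to 30.9%). At those correlations the study would be well short of 80% power under either method. The shift avoided per one-SE baseline imbalance runs from 1.5 points (r = 0.90) to 7.7 points (r = 0.5). These figures assume equal SDs of 50, a linear relation to baseline and full data on 16 and 32 patients.

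The mismatch between Mann-Whitney and the stated aim of comparing mean changes does not depend on r, and is reason enough to fix the method for each outcome in advance.

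**What to change.** In the statistical analysis plan, before the data are analysed:

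- For each continuous secondary outcome with a V1 value, fit the month-6 value on arm and the baseline value of the same outcome. Report the adjusted mean difference with its 95% confidence interval. Use the same model for the exploratory month-1 analysis.
- List by name the ordinal outcomes, such as the Modified Ashworth Scale and the Penn Spasm Frequency Scale, that will use a rank-based method or bootstrap intervals, and state the effect measure for each. This replaces the switch on normality.
- Do not add functional level by default. It costs two more degrees of freedom and may lower power. The Intervention section forms it from the EDSS, so for that outcome it would largely repeat the baseline covariate.
- Leave adherence and discomfort descriptive, as planned.

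The cost is one degree of freedom per model and a change of wording. No new data are needed, and SPSS, the software already chosen, can fit the model.
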